## Abstract

**Background:**

Approximately 70,000 patients/year undergo surgery for repair of a fractured hip in the United Kingdom. This is associated with 30-day mortality of 9% and survivors have a considerable length of acute hospital stay postoperatively (median 26 days). Use of oesophageal Doppler monitoring to guide intra-operative fluid administration in hip fracture repair has previously been associated with a reduction in hospital stay of 4-5 days. Most hip fracture surgery is now performed under spinal anaesthesia. Oesophageal Doppler monitoring may be unreliable in the presence of spinal anaesthesia and most patients would not tolerate the probes. An alternative method of guiding fluid administration (minimally-invasive arterial pulse contour analysis) has been shown to reduce length of stay in high-risk surgical patients but has never been studied in hip fracture surgery.

**Methods:**

Single-centre randomised controlled parallel group trial. Randomisation by website using computer generated concealed tables. Setting: University hospital in UK. Participants: 128 patients with acute primary hip fracture listed for operative repair under spinal anaesthesia and aged > 65 years. Intervention: Stroke volume guided intra-operative fluid management. Continuous measurement of SV recorded by a calibrated cardiac output monitor (LiDCOplus). Maintenance fluid and 250 ml colloid boluses given to achieve sustained 10% increases in stroke volume. Control group: fluid administration at the responsible (blinded) anaesthetist's discretion. The intervention terminates at the end of the surgical procedure and post-operative fluid management is at the responsible anaesthetist's discretion. Primary outcome: length of acute hospital stay is determined by a blinded team of clinicians. Secondary outcomes include number of complications and total cost of care.

Funding NIHR/RfPB: PB-PG-0407-13073.

**Trial registration number:**

Trial registration: Current Controlled Trials ISRCTN88284896.

## Background

Approximately 70,000 patients per year undergo surgery for repair of a fractured hip in the United Kingdom (UK) [1], at a cost of £25,424 per patient [2]. Hip fracture is associated with a high mortality (approximately 9% at 30 days postoperatively)[3] and a considerable length of acute hospital stay (median stay 26 days) [4]. Mortality and length of stay in hospital have remained relatively constant over recent years. The majority of patients with hip fracture are elderly women (median age 81 years, 73% female) [2], and the number of these patients will likely increase in the future in line with the changes in the United Kingdom population [5-7].

Patients with hip fracture suffer from a variety of fluid losses following their injury. They spend a variable amount of time unable to drink or eat, due to immobility at the time of injury and fasting prior to surgery. The fracture itself will haemorrhage internally to a variable degree and there may clinically important blood loss both during and after surgery [8]. Many elderly patients are taking medications which promote fluid loss (mainly diuretics) [9]. For these reasons most patients are given intravenous fluid on admission. During surgery the anaesthetist usually gives intravenous fluids based upon clinical judgement of all the above factors and clinical signs such as heart rate and blood pressure.

The amount of intravenous fluid patients are given before, during and after surgery, may have prolonged effects on outcome. Studies in non-orthopaedic surgery suggest that protocol driven (or goal directed) intra-operative fluid administration is associated with improved outcome and reduction in hospital stay [10,11]. The aim of goal-directed fluid therapy is to optimise the amount of blood in the veins filling the heart and therefore optimise stroke volume (volume of blood leaving the heart with every heart beat), cardiac output (volume of blood pumped by the heart per minute) and thereby oxygen delivery to the tissues. A number of studies suggest that derangement of cardiac output is one factor that is strongly associated with post-operative complications and death [12]. Previous studies of patients undergoing surgery for fractured hip have shown that using a Doppler ultrasound probe placed in an anaesthetised patient's oesophagus to measure the velocity of blood flow in the aorta to help guide fluid administration, resulted in a reduced hospital stay from 17 to 12 days [13-15]. Administering a fixed dose of additional fluid without cardiac output monitoring does not seem to be of benefit [16]. However, many patients receive a spinal anaesthetic for hip surgery, a technique which is associated with a lower risk of heart attack, confusion and low blood oxygen levels compared to general anaesthesia [17]. During spinal anaesthesia, the patient remains awake or lightly sedated and therefore would be unlikely to tolerate an ultrasound probe in their oesophagus [18]. The ultrasound measurements of cardiac output may also be unreliable when a spinal anaesthetic is used [19].

An alternative to the Doppler ultrasound probe is estimation of cardiac output by analysis of the waveform of the arterial blood pressure pulse. This technique has become more practical and widespread in recent years due to advances in technology. It is a minimally invasive technique, well tolerated in awake or sedated patients, which analyses arterial pressure changes during the cardiac cycle, allowing calculation of stroke volume and cardiac output [20]. This technique has been used to guide the volume of intravenous fluid administered to patients at high risk of complications after major surgery, and when used resulted in a shorter hospital stay [21]. It has never been studied in patients having hip fractures repaired to the author's knowledge, based on literature review (including an updated systematic search based upon Parker [16], and discussion with peers). In the period since the original papers demonstrating benefits of goal-directed fluid therapy in hip fracture, other practices have also changed. More patients are given intravenous fluids as soon as they are admitted, the time to surgery has decreased and more patients have surgery performed under spinal anaesthesia. It is therefore appropriate to investigate whether goal-directed fluid management is of benefit in contemporary hip fracture care.

In addition, to the authors' knowledge the changes in the heart and blood vessels produced by a spinal anaesthetic in patients with fractured hips have never been characterised fully. Patients with a fractured hip are often elderly with numerous associated medical problems. Knowledge of how spinal anaesthetics affect the heart and blood vessels in this high risk population may help guide how to best maintain the patient's blood pressure and blood flow during surgery.

## Methods

### Study Objectives

#### Primary Aims

To investigate whether stroke volume (SV) guided fluid therapy for patients undergoing fractured hip surgery under a spinal anaesthetic affects:

1) the time the patient spends in acute care in hospital;

#### Secondary Aims

2) To investigate if using SV guided fluid therapy a patient receives while having their fractured hip repaired under a spinal anaesthetic affects:

a. the time until the patient is medically well enough to be discharged from hospital;

b. the number of postoperative complications;

c. the total amount of intravenous fluid given during surgery;

d. the total cost of care.

3) To characterise the changes in the way the heart and blood vessels work after a spinal anaesthetic, as measured by minimally-invasive cardiac output monitoring.

### Study Design

This is a prospective, single-centre, randomised, parallel group controlled trial conducted at the Queens Medical Centre campus of Nottingham University Hospitals, Nottingham, UK. Study recruitment commenced on 9^th ^September 2009 when the first patient was randomised. Recruitment is ongoing (August 2011).

### Randomization and Blinding

Randomisation (on a one-to-one allocation basis) is via a password-protected web based randomisation service provided by the Clinical Trials Support Unit and the sequence not revealed until datalock. To achieve similar numbers and balance on risk, patients will be stratified according to predicted 30-day mortality (2 levels). The Nottingham Hip Fracture Score [22-24], is used to identify patients with low (≤ 10%) or high (> 10%) risk of mortality within 30-days. Subjects are randomised on arrival in the anaesthetic room to minimise the risk of medical or surgical cancellation after randomisation.

Patients, orthopaedic surgeons and ward staff are blinded to the treatment intervention. The operative attending anaesthetist is not blinded to the treatment arm, but is blinded to the cardiac output measurements for the control arm. Postoperative data collection is by a research nurse blinded to treatment allocation. The decision that a patient is medically fit for discharge is made by the multiprofessional team when all are satisfied that the participant has no ongoing needs for acute hospital care. This team is blinded to participant allocation.

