### Study Intervention

On arrival in the anaesthetic room, all participants have an arterial line sited at the wrist using local anaesthetic and an arterial blood sample taken (to determine sodium and haemoglobin concentrations for calibration of the LiDCOplus monitor). A cannula is inserted into a peripheral vein for calibration purposes and to allow fluid administration, if there is not an adequate one already in place. The arterial line is then connected to the LiDCOplus machine and calibration performed according to the manufacturer's guidelines, using a bolus intravenous injection of lithium [36]. Routine anaesthetic monitoring is instituted by the attending anaesthetist. The spinal anaesthetic is then performed and the patient remains in the anaesthetic room for at least 10 minutes to allow collection the post-spinal anaesthetic data from the LiDCOplus monitor. The patient is then taken into theatre once the anaesthetist is satisfied that the spinal anaesthetic is adequate for surgery.

The management of fluids during the operation differs between the study group and the control group. The control group have the type, amount and rate of their intravenous fluids determined by the anaesthetist, in accordance with their usual practice. The anaesthetist is blinded to the LiDCOplus measurements by placing the LiDCO screen where it is not visible and turning off the arterial waveform display. All intra-operative fluid boluses and drugs administered by the anaesthetist, including timings, are recorded by the Investigator.

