### Sample size and justification

Previous studies of optimisation strategies have demonstrated approximately 30% reduction on acute length of stay or time until medically fit to discharge and approaches towards 50% reductions in complications in survivors.

Length of acute hospital stay in our unit is consistently around 17 days (SD 4.9 days), so to find a 3 day reduction in LOS in survivors would require 58 patients in each group with 90% power and α = 0.05. Assuming a 10% drop out rate (conversion to general anaesthesia, operative cancellation after randomisation etc.) we aim to randomize 64 subjects in each group. This would also provide the same power to find a 50% reduction in complication rates between the two groups. The study will not be powered to demonstrate differences in mortality (a 50% reduction in 30-day mortality from 10% to 5%, would require around 450 patients in each group).

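### Randomisation on reaching the anaesthetic room is earlier than the design needs, so failed calibration or early conversion to general anaesthesia becomes a post-randomisation loss with the arm known

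*Protocol article*

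**What the plan says.** All references are to the protocol article.

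- **Timing.** Randomization and Blinding: "Subjects are randomised on arrival in the anaesthetic room to minimise the risk of medical or surgical cancellation after randomisation".
- **Who knows the arm.** Same section: "The operative attending anaesthetist is not blinded to the treatment arm, but is blinded to the cardiac output measurements for the control arm". Patients, surgeons, ward staff, the research nurse who collects postoperative data and the team that decides fitness for discharge are all blinded.
- **Common steps.** Study Intervention opens with "On arrival in the anaesthetic room, all participants have an arterial line sited at the wrist using local anaesthetic". Then comes "calibration performed according to the manufacturer's guidelines, using a bolus intravenous injection of lithium", and after it "Routine anaesthetic monitoring is instituted by the attending anaesthetist". The spinal follows, with at least 10 minutes of recording. The patient goes to theatre once the anaesthetist accepts the block as adequate.
- **Where the arms part.** Same section: "The management of fluids during the operation differs between the study group and the control group".
- **Expected losses.** Sample size and justification: "Assuming a 10% drop out rate (conversion to general anaesthesia, operative cancellation after randomisation etc".
- **Who is analysed.** Definition of datasets analysed limits the full analysis set to randomised patients who had LiDCOplus monitoring during surgery and whose death and discharge data are available. It rules out the intention-to-treat set for efficacy.
- **What data exist.** Selection and withdrawal of participants (Recruitment) says discharge and mortality data are collected routinely, and so exist for everyone randomised.

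**The concern.** Nothing in the shared sequence requires the allocation to be known. Making it at the start of that sequence has two consequences.

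First, a patient whose monitor cannot be calibrated, or whose spinal proves inadequate before theatre, has already been randomised. With a later allocation that patient would never have entered the trial. As planned, the patient is a loss, and the analysis-set definitions can turn the loss into an exclusion.

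Second, the person who judges the spinal adequate is not blinded to the arm. Both that judgement and care before theatre could differ between arms before the intended contrast begins.

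At stake is the comparability of the arms for length of stay. If the patients removed differ in number or in type between arms, randomisation no longer protects the comparison. Blinded outcome assessment does not repair this, because the selection happens earlier.

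**Working it through.** **1. The sequence, step by step (Randomization and Blinding; Study Intervention)**

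| Step | Same in both arms? | Person named |
|---|---|---|
| Randomisation, on arrival | n/a | none (web service) |
| Arterial line, on arrival | yes | none |
| Lithium calibration | yes | none |
| Routine monitoring | yes | attending anaesthetist |
| Spinal | yes | none |
| At least 10 minutes of recording | yes | none |
| Spinal judged adequate | yes | anaesthetist |
| Intra-operative fluids | **no** | anaesthetist (control); protocol algorithm with anaesthetist's discretion (intervention) |

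The order of the first two rows is not given. Calibration and everything below it come after arrival, and so after randomisation as written.

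**2. The plan's own sample size**

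Inputs from Sample size and justification: difference 3 days, SD 4.9 days, power 90%, α = 0.05 (two-sided assumed).

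- Normal approximation: n = 2(1.960 + 1.282)² × 4.9² / 3² = 56.1, so 57 per group.
- t-test: power is 0.8998 at 57 and 0.905 at 58, so 58 per group. This matches the plan.
- Inflation for 10% loss: 58/0.9 = 64.4, so 65; 58 × 1.1 = 63.8, so 64. The plan's 64 is reproduced to within one patient. There is no sample-size error here.

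**3. Size of the loss allowance**

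64 − 58 = 6 per arm, or 12 of 128 (9.4%). A full 10% of 128 is 12.8. The section names conversion to general anaesthesia and cancellation, then leaves the list open. It gives no split by cause or timing. The share that later randomisation would prevent therefore lies between 0 and about 12 patients.

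**4. Effect on power** (64 randomised per arm, normal approximation, on the scale of days that the plan uses)

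Power = Φ(3 / (4.9√(2/m)) − 1.960), where m is the number evaluable per arm.

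| Loss | m | Power |
|---|---|---|
| 10% | 57.6 | 90.8% |
| 5% | 60.8 | 92.2% |
| 2% | 62.7 | 92.9% |
| 0% | 64 | 93.4% |

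Removing every loss gains under 3 percentage points.

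**5. Effect on bias (illustration; both inputs assumed)**

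Suppose one arm alone loses 6 of 64, and those patients would have stayed 5 to 10 days longer than the other 58. Dropping them moves that arm's mean by 6/64 × 5 = 0.47 to 6/64 × 10 = 0.94 days, against a target effect of 3 days. If both arms lose similar patients in equal numbers, the shift is nil.

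**6. How a loss becomes an exclusion**

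A randomised patient operated on without the monitor leaves the full analysis set by definition. A patient converted to general anaesthesia but still monitored meets that definition, yet may leave the per protocol set if conversion counts as a major violation. In both cases the routine outcome data remain available. The bias thus arises from early allocation and restricted analysis sets acting together.

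**The case against.** The case for the present design is a fair one.

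- **The stated reason is sound as far as it goes.** Patients are recruited on the ward, and waiting until the anaesthetic room avoids most cancellations. A reader might infer that the section contradicts itself. It does not: its reason concerns cancellation, and a later point would serve the same purpose further.
- **The text does not support the strongest account of events.** A reader might infer that allocation precedes the arterial line and that the unblinded anaesthetist carries out every preparatory step. The line and randomisation are both placed at arrival with no order given. The anaesthetist is named only for routine monitoring and for accepting the spinal. Nor does the article say exactly when the anaesthetist learns the arm.
- **The analysis set drives the bias from losses.** If everyone randomised were analysed as allocated, early losses would dilute the effect but would not select patients. It would be wrong to say that the timing biases the result whichever set is used.
- **Baseline stroke volume and the haemodynamic aim are weak grounds.** The stroke volume target applies only in the intervention arm, and the aim of characterising changes after a spinal is not a comparison between arms.
- **Early co-intervention is speculative.** The anaesthetist must know the arm during surgery in any case and may depart from the algorithm. A few earlier minutes may add little.
- **A mid-trial change has a price.** Recruitment began in September 2009 and was continuing in August 2011. Later patients would be selected on successful calibration and an adequate spinal; earlier ones were not.

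These points narrow the concern. What stands is that allocation precedes several shared steps at which patients can drop out, that an anaesthetist not blinded to the arm makes one of the decisions, and that the analysis rules can exclude those patients.

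**Conclusion.** The point holds as a design weakness that is cheap to reduce, not as a demonstrated bias. Randomisation comes earlier than the design needs, and together with the analysis-set rules it exposes the efficacy comparison to exclusions made with the arm known.

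The whole loss allowance is about 12 of 128 patients. A reader might take all 12 as avoidable; the article does not support that, because the allowance is undivided and includes cancellations, and conversions after entry to theatre would remain. Failed lines and failed calibration are not named in it at all. The effect on power is small (90.8% to 93.4%). The possible effect on the estimate, about 0.5 to 0.9 days in the illustration, rests wholly on assumed one-sided loss and assumed longer stays.

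The conclusion assumes that the anaesthetist learns the arm at or soon after randomisation; nothing in the article keeps it from them until theatre.

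**What to change.** **Timing, for patients still to be recruited.** In Randomization and Blinding, place web randomisation after calibration, completion of the post-spinal recording and the anaesthetist's confirmation that the spinal is adequate, immediately before transfer to theatre. Keep the monitor out of the anaesthetist's view in all patients until then. Apply the change to both arms from one date. The article plans no interim analysis, so this can be done without sight of results.

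**Analysis, for all patients.** In Definition of datasets analysed, make the primary efficacy comparison on all randomised patients as allocated, subject to the withdrawal provisions under Informed consent. This covers losses under the present timing and later conversions, which the timing change cannot reach. Discharge and mortality data are routine; confirm that the date of fitness for discharge is also recorded for everyone randomised.

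**Reporting.** Show numbers, losses and reasons by arm and by randomisation timing.

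**Cost.** The timing change needs a protocol amendment, and web allocation must fit in just before transfer. A few patients will have the arterial line and lithium calibration without being randomised. The trial will contain two entry points. The benefit is limited to remaining patients, whose number the article does not give; if recruitment has ended, only the analysis and reporting changes apply. Analysing everyone may dilute the effect: if 10% of patients had no benefit (assumed), the 3-day effect becomes 3 × 0.9 = 2.7 days, and power with 64 per arm is 87.6%.

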### Selection and withdrawal of participants

#### Recruitment

Participants are identified by their presence on surgical lists and are recruited from the trauma wards. The investigator informs the participant or their nominated representative (other individual or other body with appropriate jurisdiction), of all aspects pertaining to participation in the study. Participation in the study is for the duration of the anaesthetic and surgical procedure, which is approximately two hours. The study intervention is complete at the end of the surgical procedure, though all participants have a follow-up visit the next day to ensure no problems have arisen. The medical notes are reviewed following hospital discharge for in-hospital complications and medication use.

Participants are informed that entry into the trial is voluntary and that they are free to withdraw at anytime without effect on subsequent care. Data on time to discharge and postoperative mortality are collected routinely and separate from this study. These outcome data are therefore available for all randomised participants.

Included in the trial are adults incapable of providing their own consent, since a large proportion of potential subjects will be acutely or chronically confused (around 30%). Exclusion of these patients from the trial would severely limit the applicability of results to clinical practice, since these patients are more likely to die, remain in hospital for longer, and have more complications [22,25-27].

Patients from whom consent cannot be obtained due to a language barrier are not recruited to the study. This is due to the emergency nature of the surgery meaning that it would not be practical to arrange for the provision of translation services. In practice this is a very small proportion of the total elderly population in the study centre.

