### Informed consent

The capacity for consent is assessed routinely by the orthopaedic team, who decide whether the patient is competent to provide consent for the surgical procedure. If they deem the patient is unable to consent for their surgery, then the patient will be deemed incapable of providing consent to enter the study, and assent from their next of kin is sought (or nominated consultee). The capacity for consent may fluctuate in the population being studied. A member of the research team also performs an additional check of the participant's ability to consent, immediately prior to starting the study. All members of the research team are trained at taking consent in accordance with ICH-GCP guidance [28].

All patients are visited postoperatively. If the patient had had a transient impairment of their ability to consent, which has subsequently resolved, retrospective consent is sought from the patient to use their data in the study. If the patient declines, date of discharge and postoperative mortality data are collected as part of routine clinical management and so will be available for analysis. The same would occur if contact with the next of kin pre-operatively had not been possible. If the next of kin subsequently declined assent, the patient data would once again be withdrawn from the study.

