### Statistics

Data will be analysed by the research team in conjunction with a medical statistician, using latest versions of StatXact software. There will be no interim analysis.

From previous examination of the Nottingham Hip Fracture Database (which has over 7000 patients) it is expected that the primary outcome, length of stay (LOS), will be normally distributed following a log transformation. Following transformation these data will be analysed using ANOVA using the stratification risk categories. The primary outcome measure is time until declared medically fit for discharge. Length of acute hospital stay, superspell (total time in hospital including rehabilitation) will be analysed similarly.

The secondary outcomes of complications, residence and place of discharge will be treated as categorical and differences between the groups will be examined using loglinear analysis. Mortality outcome will be analysed using Kaplan-Meier mortality curves and log rank tests..

All secondary variables will the presented using descriptive statistics. In addition to the calculated values, confidence intervals and odds-ratios will be presented when appropriate. All clinical information including all adverse events will be presented in full. All secondary analyses will be interpreted with caution as the sample size calculation is based on the primary outcomes only. However, the level of power associated with secondary results will be investigated.

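### The length-of-stay ANOVA names only a two-level mortality-risk category, although the protocol says confusion prolongs stay and capacity is checked beforehand: a modest, cheaply avoided loss of precision

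*Protocol article*

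**What the plan says.** - **Confusion and outcome** (Methods, Recruitment). Patients who cannot consent are included on purpose, because "a large proportion of potential subjects will be acutely or chronically confused (around 30"%), and because "these patients are more likely to die, remain in hospital for longer, and have more complications". Only the direction is given, with no number of days and no rate.
- **Capacity** (Methods, Informed consent). "The capacity for consent is assessed routinely by the orthopaedic team", and a member of the research team "performs an additional check of the participant's ability to consent, immediately prior to starting the study". The same section warns that "The capacity for consent may fluctuate in the population being studied", and allows for next of kin who could not be contacted before the operation.
- **Timing and stratification** (Methods, Randomization and Blinding). "Subjects are randomised on arrival in the anaesthetic room", and "patients will be stratified according to predicted 30-day mortality (2 levels"). The levels are at most 10% and above 10% on the Nottingham Hip Fracture Score, whose components are not listed.
- **Model** (Methods, Statistics). After log transformation, "these data will be analysed using ANOVA using the stratification risk categories". Time to medically fit, acute stay and superspell are handled alike. Neither confusion nor capacity is named as a factor in these analyses, in the loglinear analysis of complications or in the log-rank test.

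**The concern.** The protocol names a baseline characteristic that is common, is known before surgery and, by its own account, is related to the main outcome. The stated model then conditions on a different variable, a dichotomised prediction of death. A two-level cut of mortality risk is not built to predict length of stay, so the part of the stay difference between confused and other patients that it misses remains in the error term. The standard error of the treatment comparison is then larger than it need be.

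Timing matters as well. If the arms turn out uneven on confusion and nothing was pre-specified, an adjustment chosen afterwards will look driven by the data.

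**Working it through.** **Inputs from the protocol article.** Mean stay 17 days, SD 4.9, target difference 3 days, 58 per group, 90% power, alpha 0.05 (Sample size and justification). Share confused 0.30 (Recruitment). Allocation one to one.

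**Assumed input.** The extra stay *d* of confused patients is not in the document. The range taken is 1 to 3 days, with 5 days as a high case.

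**1. The plan's own figure.** n = 2 × (1.960 + 1.282)² × 4.9² / 3² = 56.1, so 57 per group by the normal approximation. The t-based solution is 57.04, so 58. The stated 58 is reproduced as a two-sided calculation (one-sided gives 46), and 58 × 1.1 = 63.8 gives the stated 64. Power at 58 per arm is 90.9%. The standard error is 4.9 × √(2/58) = 0.910 day. None of this depends on using confusion.

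**2. Variance that adjustment could remove.** The share of variance due to a factor present in 30% of patients is R² = 0.3 × 0.7 × d² / 4.9², and the residual SD is 4.9 × √(1 − R²).

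| Assumed *d* (days) | R² | Residual SD | SE (days) | n per group for 90% | Power at 58 |
|---|---|---|---|---|---|
| none (as planned) | 0 | 4.90 | 0.910 | 57 | 90.9% |
| 1 | 0.9% | 4.88 | 0.906 | 56 | 91.2% |
| 2 | 3.5% | 4.81 | 0.894 | 55 | 91.9% |
| 3 | 7.9% | 4.70 | 0.873 | 52 | 93.0% |
| 5 | 21.9% | 4.33 | 0.804 | 44 | 96.2% |

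These gains are upper bounds, because they treat the risk category as carrying no information on confusion.

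**3. Cross-check on the log scale,** where the analysis is planned. The log SD implied by 17 and 4.9 is √ln(1 + (4.9/17)²) = 0.283, so its square is 0.0798. For an assumed ratio of stays *r*, R² = 0.21 × (ln r)² / 0.0798. This gives 2.4% at r = 1.1, 8.7% at 1.2 and 18.1% at 1.3. On a stay of 17 days these ratios correspond to about 1.7, 3.4 and 5.1 extra days, so the two scales agree in size.

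**4. Chance imbalance.** With no balancing, the between-arm difference in the share confused has SD √(2 × 0.3 × 0.7/58) = 8.5 points. A difference of 10 points or more has exact probability 0.26 at 58 per arm and 0.21 at 64. At d = 3, 10 points shift the estimate by 0.3 day, against a standard error of 0.91 day.

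**5. Is that shift bias?** At d = 3 the variance of the shift is 3² × 0.42/58 = 0.065. The drop in the squared standard error from adjustment is 4.9² × (2/58) × 0.079 = 0.065. They are the same quantity: the unadjusted standard error already contains the imbalance.

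**The case against.** Four objections have force.

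- **The strata may already use confusion.** A reader might infer that neither the stratification nor the analysis makes any use of it. The article does not show this. The score predicts death, confused patients are said to die more often, and one cited source (reference 22) supports both the score and the statement about confused patients. With the components unlisted, the overlap could be full, partial or nil. This stands. What survives is that a two-level mortality cut need not capture an effect on length of stay.
- **Chance imbalance is not bias.** A reader might infer that an uneven split would be mistaken for a treatment effect. Under randomisation the type I error and the confidence interval already allow for it, as step 5 shows. This stands, and the point is confined to precision.
- **Consent status is a poor variable.** A reader might take own consent versus assent as complete and clean. The Informed consent section does not support this: some next of kin cannot be reached, capacity can fluctuate and the two assessments may disagree. This also stands, so the factor should be the capacity assessment itself. Even then it is a proxy for confusion.
- **Further covariates may sit in an analysis plan that is not shown.** Their absence from an article is not an omission, and adjusting for the stratification factor is standard practice. This limits the point to a suggestion about the model as stated.

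**Conclusion.** The point holds as a modest loss of efficiency. The stated length-of-stay model rests on one dichotomised mortality-risk factor and does not name a baseline characteristic that the protocol itself calls prognostic for stay.

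For assumed differences of 1 to 3 days the avoidable variance is at most about 1% to 8%, and power at 58 per arm moves from about 91% to 91–93%. Only at a difference of about 5 days does the gain become substantial (R² 22%, power 96%). The planned sample size stands either way.

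These figures rest on four assumptions: the assumed *d*; a 30% share that the article gives for potential subjects rather than those enrolled; the article's SD of 4.9 days; and no overlap between the risk category and confusion. Overlap, or misclassification of confusion by capacity, would shrink the gain. The documents do not support a claim that the primary comparison is biased or that the design ignores confusion altogether.

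**What to change.** Before datalock, pre-specify capacity before randomisation as a second factor beside the risk category in the ANOVAs of log time to medically fit, log acute stay and log superspell. Define it as has or lacks capacity at the research team's check immediately before the study starts, regardless of whether next of kin could be reached. Do not use recovery of capacity after surgery. State whether the Nottingham Hip Fracture Score includes a cognitive item, so that the expected overlap is clear. Use of the factor in the complication and mortality analyses is optional.

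The cost is analysis wording and one degree of freedom, with no new patients or procedures. One practical condition is that the result of the check has been recorded for patients already randomised, which the article does not say. The change can still be made without knowledge of results: the article reports recruitment as ongoing, plans no interim analysis and keeps the sequence concealed until datalock.
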